### Power calculations

The sample size and statistical power for this 4-arm parallel-group randomized controlled trial is analyzed for various scenarios based on a range of likely magnitudes of outcomes for asthma-related health outcome and environmental exposure assessments (Table 1). Calculations are made utilizing a robust statistical software tool, G*Power ver. 3.1.9.7, for a repeated measures ANOVA with a within-between interaction [49]. A range of effect sizes from small (Cohen’s f = 0.10), medium (f = 0.25), to large (f = 0.40) are considered to accommodate varying expected intervention effects, ensuring both robustness and generalizability of the findings [50]. Sample size calculations were conducted for the health outcomes (ACT and PFT) and environmental outcomes (IAQ and mold measurements). Required sample sizes were estimated based on expected effect sizes to achieve a statistical power >0.80 and adjusted for a 10% dropout rate. For monthly ACT surveys (n = 24) and monthly average low-cost IAQ measurements (n = 24), the required sample sizes ranged from 84 households for a small effect size (0.10) to 9 households for a large effect size (0.40). For PFT and mold measurements, the required sample sizes were estimated at 220 and 308 households, respectively, for detecting a small effect size (0.10); 40 and 53 households, respectively, for a medium effect size (0.25); and 18 and 26 households, respectively, for a large effect size (0.40). Although larger sample sizes were required to detect a small effect size (0.1) for PFT and mold, these estimates represent the sample sizes needed to detect very small changes. Further, the AIRVAC study was primarily designed to evaluate intervention effects on asthma outcomes and IAQ, for which the estimated sample sizes were within the planned recruitment range. Therefore, the final target sample size was set at 80 households, with an initial recruitment target of 88 households to account for potential dropout.

**Table 1 pone.0358221.t001:** Sample size calculations.

Effect Size (Cohen’s f for ANOVA)	Small			Medium			Large
	0.1	0.15	0.2	0.25	0.3	0.35	0.4

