### Health outcome assessments

#### Primary outcome measures.

We will use the following measures to assess asthma control:

Asthma Control Test (ACT): Monthly ACT surveys will be administered electronically using an online survey link distributed to participants. The ACT is a 5-item, clinically validated questionnaire designed to assess the multi-dimensional nature of asthma control, including asthma symptoms, use of rescue medications, and the impact of asthma on daily functioning [38]. ACT scores range from 5 (“poor control of asthma”) to 25 (“complete control of asthma”), with a cut-off of 19 used to identify participants with suboptimal asthma control according to the Global Initiative for Asthma (GINA) guidelines: a score >19 indicates “well-controlled asthma,” whereas a score ≤19 indicates “poorly controlled asthma” [39,40]. Children under 12 years of age will complete the Childhood Asthma Control Test (C-ACT).Asthma Control Questionnaire (ACQ): In addition to monthly ACT, we will administer the ACQ during the home visits (V1-V4) to assess asthma control more comprehensively. The ACQ consists of 7 items covering asthma symptoms, rescue bronchodilator use, and lung function (FEV_1_, forced expiratory volume in one second, FEV_1_). Each scored on a 7-point scale from 0 (“no impairment”) to 6 (“maximum impairment”), and the overall score is calculated as the mean of all items, with lower scores indicating better control. Consistent with established guidelines, an ACQ score ≤0.75 will be used to identify “well-controlled asthma,” whereas a score ≥1.50 will indicate “poorly controlled asthma,” with intermediate values reflecting partially controlled asthma [41,42].

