**Pulmonary Function Testing (No. of measurements = 4)**							
Statistical Power	0.8	0.81	0.8	0.83	0.86	0.83	0.82
Sample Size Per Group	50	23	13	9	7	5	4
Total Sample Size	200	92	52	36	28	20	16
Total Sample Size (adjusted for 10% dropout)	**220**	101	57	**40**	31	22	**18**

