**Mold Measurements (No. of measurements = 2, baseline & end-line)**							
Statistical Power	0.81	0.81	0.82	0.8	0.82	0.83	0.86
Sample Size Per Group	70	32	19	12	9	7	6
Total Sample Size	280	128	76	48	36	28	24
Total Sample Size (adjusted for 10% dropout)	**308**	141	84	**53**	40	31	**26**

Sample sizes were calculated based on repeated measures ANOVA (α = 0.05, power = 0.80) and expected effect sizes, with adjustment for a 10% dropout rate.

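### The sample-size rationale speaks of asthma outcomes, but only the monthly ACT was sized; the ACQ, also primary, has four measurements and falls outside 80/88 households for small effects

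*Protocol article*

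**What the plan says.** Under Primary outcome measures, the article lists two measures of asthma control. The first is the ACT, surveyed monthly. The second follows at once: "In addition to monthly ACT, we will administer the ACQ during the home visits (V1-V4". The secondary measures, spirometry among them, come in a separate section and share the V1 to V4 schedule. Nothing in the text ranks the ACQ below the ACT.

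Under Power calculations, the outcomes that were sized are named: "Sample size calculations were conducted for the health outcomes (ACT and PFT) and environmental outcomes (IAQ and mold measurements". The ACQ is not among them. Table 1 has three blocks: ACT and IAQ with 24 measurements, "Pulmonary Function Testing (No. of measurements = 4", and mold with two. For the ACT and IAQ block, "the required sample sizes ranged from 84 households for a small effect size (0.10) to 9 households for a large effect size (0.40".

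The same section concedes that spirometry and mold need more households than planned at f = 0.10. It then says that the study was "primarily designed to evaluate intervention effects on asthma outcomes and IAQ, for which the estimated sample sizes were within the planned recruitment range", and from this sets the target at 80 households, with 88 recruited.

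**The concern.** The sentence that carries the choice of N refers to asthma outcomes as a class, while the calculation behind it covers one of the two primary asthma-control measures. A secondary outcome (spirometry) has a row in Table 1; a primary one (ACQ) has none. The two share a visit schedule, so the limitation the article concedes for spirometry at small effects applies to the ACQ under the same planning settings, yet the wording places asthma outcomes on the favourable side of that contrast.

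At stake is how an ACQ result will be read. A null ACQ finding could be taken as coming from a primary outcome that the sample size was chosen to cover, although for small effects the design does not give it that sensitivity. Data collection had not begun when the article was written, so the rationale can be corrected before any result is known.

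**Working it through.** **Inputs from the article.** Test: "for a repeated measures ANOVA with a within-between interaction" in G*Power 3.1.9.7. Groups: k = 4. Table 1 footnote: "Sample sizes were calculated based on repeated measures ANOVA (α = 0.05, power = 0.80) and expected effect sizes". Measurements: m = 24 for ACT and IAQ, m = 4 for spirometry, and m = 4 for the ACQ (V1 to V4). Planned N: 80, with 88 recruited.

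**Inputs not in the article.** The correlation among repeated measures (ρ) and the non-sphericity factor (ε) are not given. I assume ρ = 0.5 and ε = 1 because they reproduce Table 1, and vary both below.

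**Formula** (noncentral F, within-between interaction):

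- λ = f² · N · m · ε / (1 − ρ)
- df1 = (k − 1)(m − 1)ε
- df2 = (N − k)(m − 1)ε
- power = P(F′ > F critical at 0.05)

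**Step 1: reproduce Table 1.**

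- m = 24, N = 76, f = 0.10: λ = 0.01 × 76 × 24 / 0.5 = 36.48, df 69 and 1656, power 0.815 (printed 0.82).
- m = 4, N = 200, f = 0.10: λ = 0.01 × 200 × 4 / 0.5 = 16.0, df 9 and 588, power 0.804 (printed 0.80).

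All 21 sample sizes in the table reproduce as the smallest balanced N. Twenty of the 21 powers agree with the printed values; the exception (m = 24, f = 0.40: 0.898 against 0.92) has no bearing here.

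**Step 2: read the four-measurement row for the ACQ.** In this calculation N depends on k, m, f, ρ, ε, α and power, not on which outcome is measured. With the same planning settings, the spirometry row is therefore the ACQ row.

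| f | Total N | With dropout | Against 80 / 88 |
|---|---|---|---|
| 0.10 | 200 | 220 | above both |
| 0.15 | 92 | 101 | above both |
| 0.20 | 52 | 57 | within |

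**Step 3: ACQ power at the planned N** (m = 4, ρ = 0.5, ε = 1; at N = 80, df 9 and 228).

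- f = 0.10: λ = 0.01 × 80 × 4 / 0.5 = 6.4, power 0.349 (0.386 at N = 88).
- f = 0.15: λ = 0.0225 × 80 × 4 / 0.5 = 14.4, power 0.739.
- f = 0.20: λ = 0.04 × 80 × 4 / 0.5 = 25.6, power 0.960.
- Smallest f with 80% power: about 0.159 at N = 80 and 0.152 at N = 88.

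For comparison, the ACT at N = 80 and f = 0.10 has λ = 0.01 × 80 × 24 / 0.5 = 38.4 and power 0.844.

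**Step 4: sensitivity to the unstated settings** (N = 80, f = 0.10).

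| ρ (ε = 1) | 0.3 | 0.5 | 0.6 | 0.7 | 0.8 | 0.9 |
|---|---|---|---|---|---|---|
| ACQ power | 0.25 | 0.35 | 0.44 | 0.58 | 0.79 | 0.99 |

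| ε (ρ = 0.5) | 1 | 0.75 | 0.5 |
|---|---|---|---|
| ACQ power | 0.35 | 0.295 | 0.24 |
| ACT power | 0.84 | 0.75 | 0.61 |

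**Step 5: where f = 0.10 comes from.** No single design effect is named. In the 24-measurement block, f = 0.10 gives 84 households after dropout and f = 0.15 gives 40. Only the first is near 80 to 88, and the contrast with spirometry and mold is also drawn at 0.10. The effect is implied, not stated.

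**The case against.** The strongest reply is that the article makes no power claim for the ACQ. It first says which health outcomes were sized (ACT and spirometry), and its rationale speaks of outcomes that have an estimate. Read that way, the sentence is true of the ACT and IAQ, since 84 lies between 80 and 88. The four-measurement figures are also printed in full, with the need for larger samples at f = 0.10 conceded for spirometry and described as concerning very small changes. At f = 0.20 or more, a four-measurement outcome is well powered at 80 households.

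Much of this stands. A reader might infer that the article promises detection of f = 0.10 on the ACQ and delivers about 35% power. The text does not support that: it surveys f from 0.10 to 0.40, names no design effect and gives no ACQ figure. The 35% also depends on a correlation and sphericity that the article does not state. Nor is there an arithmetic error in the required sample sizes of Table 1, and no passage plans to read a null ACQ as adequately powered.

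What does not stand is that the wording is harmless. The phrase is unqualified, the ACQ is listed as primary, and the sentence is the stated reason for N. Describing the ACQ as a fuller assessment of control does not remove it from the primary list.

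**Conclusion.** The point holds as an inconsistency between the primary outcome list and the sample-size rationale; it should be fixed. The stated coverage extends to the monthly ACT and IAQ. It does not extend to the ACQ for small effects: at f = 0.10 and 0.15 the article's own four-measurement row exceeds both 80 and 88.

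Under the settings that reproduce Table 1, the shortfall is confined to f below about 0.16. Its size at f = 0.10 is conditional: 0.25 to 0.79 over correlations of 0.3 to 0.8, and adequate only if the correlation is higher still. The ACT figure at f = 0.10 is conditional too, and drops below 0.80 once sphericity is relaxed to ε = 0.75. Neither figure should be stated without its assumptions.

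**What to change.** In Power calculations and Table 1:

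1. Limit the rationale sentence to the monthly ACT and IAQ.
2. Label the four-measurement block of Table 1 as applying to the ACQ as well as spirometry. Its numbers do not change.
3. State the correlation and sphericity used in the calculations. If they were ρ = 0.5 and ε = 1, say so.
4. State that, under those assumptions, 80 households give the ACQ 80% power only for f of about 0.16 or larger.
5. Attach the same assumptions to the ACT statement at f = 0.10: at 80 households, 0.84 under sphericity, 0.75 at ε = 0.75 and 0.61 at ε = 0.5.

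The cost is one table label and a few sentences. No households are added, and neither the design nor the analysis changes. The stated sensitivity for the ACQ becomes less favourable.

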The primary analyses will follow the intention-to-treat (ITT) principle, including all randomized households analyzed according to their assigned intervention group, to evaluate the effects of ERVs and portable HEPA air cleaners on IAQ, mold reduction, and asthma-related health outcomes by comparing the intervention and control (sham) groups using repeated measures analysis of variance (ANOVA) with a within-between interaction. Pairwise comparisons will be conducted between each intervention and control group (Group 1 vs. Group 2, Group 3 vs. Group 4) and between intervention groups (Group 1 vs. Group 3), using Tukey’s Honest Significant Difference (HSD) test to adjust for multiple comparisons. Repeated monthly ACT scores will be analyzed using multivariate mixed-effects models to account for within-subject correlations over time. Per-protocol (PP) analyses will be conducted as sensitivity analyses and will include only households that adequately adhered to the assigned intervention protocol. Intervention adherence will be assessed using plug load logger data for both ERV and air cleaner units, including device operation status and operating duration [52]. Additionally, subgroup analyses will be conducted to explore whether intervention effects differ by demographic and socioeconomic characteristics, baseline asthma severity, and baseline IAQ.

For secondary analyses, multivariate linear and logistic regression models will examine associations among housing characteristics, occupant behaviors, indoor environmental exposures (e.g., air pollutants and mold), and asthma-related health outcomes. Housing characteristics will be considered as potential covariates or confounders, when applicable, based on biological plausibility and statistical considerations. Prior to multivariable modeling, correlations among environmental exposure variables (e.g., PM, NO_2_, VOCs, and mold indices) will be evaluated using Pearson or Spearman correlation coefficients, depending on data distribution. Variance inflation factors (VIFs) will also be calculated to assess multicollinearity among predictors. Highly correlated exposures will not be included simultaneously in the same model to minimize multicollinearity, overfitting, and unstable estimates.

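### Table 1 gives power for the four-group omnibus interaction, not for the planned Tukey comparisons, and its coverage claim fails for the ACQ, a primary measure, at small effects

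*Protocol article*

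**What the plan says.** The Power calculations section describes a "4-arm parallel-group randomized controlled trial" and sizes it "for a repeated measures ANOVA with a within-between interaction". The footnote to Table 1 gives the remaining inputs: "Sample sizes were calculated based on repeated measures ANOVA (α = 0.05, power = 0.80) and expected effect sizes". Neither the correlation among repeated measures nor a nonsphericity correction is stated. Effect sizes run from f=0.10 to f=0.40, and no single design effect is chosen.

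Table 1 has three blocks: ACT and indoor air quality (24 measurements), pulmonary function (4) and mold (2). The text concedes that pulmonary function and mold need more than the planned number at f=0.10, adding that "these estimates represent the sample sizes needed to detect very small changes". It then says that the trial was designed mainly for asthma outcomes and air quality, "for which the estimated sample sizes were within the planned recruitment range", and sets the target at 80 households, with 88 recruited.

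The Primary outcome measures section lists two measures of asthma control. One is the monthly ACT. The other is the ACQ: "we will administer the ACQ during the home visits (V1-V4) to assess asthma control more comprehensively". No calculation is given for the ACQ.

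The Data management and statistical analysis plan section plans these tests: "Pairwise comparisons will be conducted between each intervention and control group (Group 1 vs. Group 2, Group 3 vs. Group 4"), plus Group 1 vs. Group 3, with Tukey's HSD adjustment. Monthly ACT is assigned to mixed-effects models.

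**The concern.** There are two separate mismatches.

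- **Primary outcome.** The sentence that justifies 80 households speaks of asthma outcomes in general, but one of the two primary asthma measures has the same number of measurements as the pulmonary function block, which the article concedes is short at f=0.10.
- **Test.** The trial's questions are device against its own sham and device against device. Table 1 answers a different one: whether the four group profiles differ anywhere over time. With 24 months that test has 3 × 23 = 69 numerator degrees of freedom.

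At stake is the reading of a null result. A non-significant ACQ contrast could be taken as evidence from a trial powered for small effects, when no such power was shown.

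**Working it through.** **Inputs.** From the article: four groups; alpha 0.05; f from 0.10 to 0.40; 24, 4 or 2 measurements; 80 target and 88 recruited households; 10% dropout; 40 ERV and 40 air cleaner homes. Assumed: 20 homes per arm, because the active-to-sham split is not stated.

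**1. Reproducing Table 1.** For the within-between interaction with N households and m measurements,

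λ = f²·N·m·ε/(1−ρ), df1 = 3(m−1)ε, df2 = (N−4)(m−1)ε.

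With ρ=0.5 and ε=1, all 21 tabled totals are the smallest balanced N that reaches 0.80, and 20 of 21 powers agree to two decimals. The exception is f=0.40, m=24, N=8: 0.898 against 0.92. Three cells at f=0.10:

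| Block | N | λ | Computed | Stated |
|---|---|---|---|---|
| ACT/air quality, m=24 | 76 | 0.01·76·24/0.5 = 36.5 | 0.815 | 0.82 |
| Pulmonary function, m=4 | 200 | 0.01·200·4/0.5 = 16 | 0.804 | 0.80 |
| Mold, m=2 | 280 | 0.01·280·2/0.5 = 11.2 | 0.806 | 0.81 |

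**2. ACQ (m=4), same formula.**

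| f | Households needed (with dropout), Table 1 | Power, N=80 | Power, N=88 |
|---|---|---|---|
| 0.10 | 200 (220) | 0.35 | 0.39 |
| 0.15 | 92 (101) | 0.74 | 0.79 |
| 0.20 | 52 (57) | 0.96 | 0.98 |

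With 80 homes, power reaches 0.80 at about f=0.16.

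**3. Sensitivity of the ACT figure to the unstated inputs** (N=76, f=0.10, stated 0.82). With ε=1: 0.41 at ρ=0, 0.61 at ρ=0.3, 0.98 at ρ=0.7. With ρ=0.5: 0.69 at ε=0.7 and 0.57 at ε=0.5.

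**4. Tukey active versus sham.** Assume a sustained step after installation, equal correlation ρ=0.5, and both devices equally effective. Then:

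- active-sham difference in pre-post change: δ = 4f SD, so f=0.10 is 0.40 SD;
- SD of the change: √(4(1−ρ)/m), i.e. 0.289, 0.707 and 1.000 for m = 24, 4 and 2;
- SE = SD·√(2/n); power from the noncentral t against the Tukey critical value for four groups (2.63 at 76 df).

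Example, m=4, n=20, f=0.10: SE = 0.707·√0.1 = 0.224, noncentrality 0.40/0.224 = 1.79, power 0.21.

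| Block | Stated power | Tukey power, tabled group sizes | Tukey power, n=20, f=0.10 | Detectable difference, 80% power, n=20 |
|---|---|---|---|---|
| m=24 | 0.82–0.98 | 0.84–0.99 | 0.96 | 0.32 SD |
| m=4 | 0.80–0.86 | 0.59–0.66 | 0.21 | 0.78 SD |
| m=2 | 0.80–0.86 | 0.42–0.50 | 0.09 | 1.10 SD |

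For m=24 the Tukey figure exceeds the stated one in six of seven cells.

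**5. Unequal devices.** Let the air cleaner have half the ERV effect, at the same f=0.10. The ERV effect is then 0.482 SD and the air cleaner effect 0.241 SD. With 20 per arm:

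| Comparison | m=24 | m=4 |
|---|---|---|
| ERV vs sham | 0.995 | 0.33 |
| Air cleaner vs sham | 0.51 | 0.07 |
| ERV vs air cleaner | 0.51 | 0.07 |

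**6. Serially correlated months (illustration only).** Three assumed structures have an average correlation of 0.48–0.49: 0.3+0.4·0.9^lag, 0.2+0.6·0.9^lag, and 0.9^lag. They give ε of 0.57, 0.38 and 0.18, and ACT detectable differences of about 0.64, 0.75 and 0.94 SD instead of 0.32.

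**7. Dropout.** Table 1 multiplies by 1.1. Dividing by 0.9 gives 85 for 76 (not 84), 312 for 280 (not 308) and 89 for 80 (not 88). Recruiting 88 leaves 88·0.9 = 79.2.

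**The case against.** The strongest defence is that the block that sized the trial survives. For monthly ACT and air quality, under the assumptions that reproduce Table 1 and with equally effective devices, the Tukey active-versus-sham test has more power than the stated figure almost throughout. This stands. A reader might infer that every planned comparison has far lower power than tabled; the documents do not support that. For ACT and air quality the shortfall appears only if one device is weaker or the months are serially correlated. The article gives no autocorrelation, so the size of any serial loss is an assumption. Monthly ACT is also assigned to mixed models, so a sphericity-corrected ANOVA figure is not its power.

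A second defence is that the article commits to no single effect size and openly lists the outcomes it calculated, and that the ACQ fits at f=0.20 and above. This also stands, so an unqualified statement that the ACQ is not covered would be too strong. It does not rescue the sentence, which follows directly on the concession for pulmonary function and mold at f=0.10. At that effect the ACQ is short by the same amount as pulmonary function.

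Third, the shortfall for pulmonary function and mold at f=0.10 is already conceded. That concession concerns the omnibus test, however; the gap to the Tukey tests is not disclosed.

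Finally, a condensed article may leave the correlation and epsilon to a fuller document. Their absence alone would not be a finding. They matter here because the printed power depends strongly on them. The values are recovered from the table; the documents do not say how they were chosen.

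**Conclusion.** The point holds in limited form. The coverage sentence is wrong for the ACQ below about f=0.16: at f=0.10 the article's own row requires 220 recruited households against 88, and power with 80 homes is 0.35. This needs only the article's inputs and the values (ρ=0.5, ε=1) that reproduce its table.

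Table 1 is not the power of the planned comparisons. For four-measurement outcomes and mold it overstates Tukey active-versus-sham power, given a sustained step, ρ=0.5 and equal device effects. For ACT and air quality it does not overstate it under those conditions, but neither does it show adequate power for ERV versus air cleaner or for the weaker device. The dropout slip is real and changes no decision.

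**What to change.** Keep the number of households. In the Power calculations section and Table 1:

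- Limit the sentence about the planned recruitment range to ACT and indoor air quality, and add an ACQ row with four measurements.
- Label the existing figures as power for the omnibus group-by-time interaction, and state ρ and ε with a sensitivity range.
- Add the power or detectable difference of the three planned Tukey contrasts at 20 homes per arm for ACT, ACQ, pulmonary function, air quality and mold, including a case with unequal device effects. For the monthly outcomes, show a range of serial correlation structures, marked as assumptions.
- As a minor correction, inflate for dropout by n/(1−0.10).

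The cost is one table and one paragraph rewritten, with less favourable stated power for ACQ, pulmonary function and mold. No extra homes are needed. The article says that data collection has not begun, so the change can be made before any results exist.
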